## Abstract

**Background:**

Amblyopia is the commonest visual disorder of childhood in Western societies, affecting, predominantly, spatial visual function. Treatment typically requires a period of refractive correction (‘optical treatment’) followed by occlusion: covering the nonamblyopic eye with a fabric patch for varying daily durations. Recent studies have provided insight into the optimal amount of patching (‘dose’), leading to the adoption of standardized dosing strategies, which, though an advance on previous *ad-hoc* regimens, take little account of individual patient characteristics. This trial compares the effectiveness of a standardized dosing strategy (that is, a fixed daily occlusion dose based on disease severity) with a personalized dosing strategy (derived from known treatment dose-response functions), in which an initially prescribed occlusion dose is modulated, in a systematic manner, dependent on treatment compliance.

**Methods/design:**

A total of 120 children aged between 3 and 8 years of age diagnosed with amblyopia in association with either anisometropia or strabismus, or both, will be randomized to receive either a standardized or a personalized occlusion dose regimen. To avoid confounding by the known benefits of refractive correction, participants will not be randomized until they have completed an optical treatment phase. The primary study objective is to determine whether, at trial endpoint, participants receiving a personalized dosing strategy require fewer hours of occlusion than those in receipt of a standardized dosing strategy. Secondary objectives are to quantify the relationship between observed changes in visual acuity (logMAR, logarithm of the Minimum Angle of Resolution) with age, amblyopia type, and severity of amblyopic visual acuity deficit.

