## Methods/design

### Objectives of the study

The primary study objective is to determine whether study participants in receipt of a personalized dosing strategy reach trial endpoint (optimal visual acuity) in a shorter period of time, and with reduced variance, than those in receipt of a standardized dosing strategy.

The secondary study objectives are:To determine the relationship between observed changes in logMAR visual acuity as a function of:Objectively monitored occlusion dose,Type of amblyopia,Age of participant.To determine whether compliance differs between standardized and personalized dosing strategy treatment arms.

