#### Personalized dosing strategy

In the personalized dosing strategy arm, participants are prescribed an initial occlusion dose determined by their age, type, and severity of amblyopia, based upon dose-response functions derived from previous studies involving participants of near-identical clinical and demographic status to those enrolled in the present trial [11,12]. As participants in this arm progress through the occlusion phase, the prescribed occlusion dose is modified at each clinic visit, depending on treatment compliance, and is predicated on the notion of a total effective dose: the minimum amount of occlusion that should result in an optimal visual outcome.

The rationale underpinning treatment by a personalized dosing strategy is an attempt to define a patient’s total occlusion dose, which can then be converted to a daily patching regimen on the presumption of a fixed treatment period. We make the assumption that every patient has some optimal visual outcome that they can hope to achieve, and that there exists some total effective dose of occlusion that must be received in order to achieve it. Furthermore, we assume that any dose received by a patient in excess of this total effective dose is ‘wasted’: it does not improve the patient’s visual acuity any further, as it is impossible to improve beyond the patient’s optimal visual outcome. For example, if a patient’s total effective dose is 200 hours, then that patient will have the same visual outcome after 200, 250, or even 1,000 hours of occlusion. However, the patient’s visual improvement would be limited if fewer than this 200 hours of occlusion were achieved. Employing mathematical notation, we can say that patient *i* has some optimal visual acuity *V*_*i*_^***^, which will be achieved if, and only if, patient *i* undertakes at least *D*_*i*_^***^ hours of occlusion. Our aim is to construct a model that predicts this *D*_*i*_^***^ based on an analysis of known treatment-response functions [11,12]. To constrain the complexity of the model (and in the absence of compelling evidence to the contrary) it is assumed that the total effective dose is dose-rate independent, that is, a single occlusion dose is of equivalent effectiveness to multiple individual doses that sum to the same total number of hours.

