Predictions of *D*_*i*_^***^ were derived from a normal linear interval regression model with the total effective dose of some patient *i* with initial residual amblyopia *R*_*i*_ and age *A*_*i*_ estimated by the formula:$$ {\mathrm{D}}_{\mathit{\mathsf{i}}}^{*}={\left(18.150+16.122{R}_i\hbox{--} 0135{A}_i\hbox{--} 0.547{T}_M\hbox{--} 8.028{T}_S\hbox{--} 12.176{R}_i{T}_M\hbox{--} 11.334{R}_i{T}_S+0.065{A}_i{T}_M+0.192{A}_i{T}_{\mathrm{S}}\right)}^2 $$where *T*_M_ and *T*_S_ are indicator functions taking the value 1 if the patient has mixed or strabismic amblyopia, respectively, or 0 otherwise.

In practice, participants in the personalized dosing strategy arm have their total effective dose estimated on an assumed fixed follow-up period of 12 weeks, which results in manageable dose-rates. Therefore, an individual patient’s personalized daily patching regimen will be calculated by first estimating the total effective dose and then dividing this by the number of days left in the follow-up period. For reasons of practicality, we only prescribe daily patching episodes rounded up to the nearest 30 minutes. Dose-rate can then be updated at follow-up appointments based on how much occlusion has been objectively recorded. To avoid the prescription of subtherapeutic doses of occlusion, the model is constrained such that dose-rates less than 2 hours per day are never prescribed. Of course, patients will probably be treated for a period longer than 12 weeks, as the follow-up sessions will be continued until the visual acuity criteria for study exit have been met. Therefore, once a patient passes the tenth week of follow-up, all future daily prescription calculations will assume a 2-week follow-up period until treatment is completed.

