### Endpoint determination and sample size calculation

Participants complete the trial at that point in the occlusion phase at which equal visual acuity of each eye is achieved, or if vision has stabilized (defined as three inflexions in a plot of acuity against time or remaining unchanged over three consecutive visits). All children wear occlusion for a minimum of 6 weeks before discontinuing if no significant gains in visual acuity are observed. A sample size of 60 in each arm at 95% power and with a type I error rate of 0.05 corresponds to a Cohen’s *d* statistic of 0.605. The log-transformed time to best visual acuity across MOTAS [11] and ROTAS [12] was approximately normally distributed and had a mean (standard deviation) of 4.0133 (0.801). We could therefore expect to detect a difference of around 21 days in mean time to best visual acuity in our two groups.

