#### Analyses

The primary study objective of comparing time to best visual acuity between the two treatment groups, along with the secondary objective of comparing compliance, will be analyzed via standard *t* tests (to compare length of time and compliance) and Levene’s test (to compare variance in time). Suitable nonparametric alternatives will be used should concerns arise regarding the necessary distributional assumptions for these methods. The secondary objective to determine the relationship between changes in visual acuity and dose, amblyopia type, and age, will be investigated using standard regression modelling approaches.

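### The abstract's primary objective is fewer hours of occlusion, but the protocol defines, powers and tests time to best acuity, and under its own dose model time cannot stand in for hours

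*Protocol article*

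**What the plan says.** The protocol article describes its primary question in three ways.

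- **Hours.** The abstract (Methods/design) asks whether the personalized arm will, at trial endpoint, "require fewer hours of occlusion than those in receipt of a standardized dosing strategy".
- **Time.** Objectives of the study asks whether that arm will "reach trial endpoint (optimal visual acuity) in a shorter period of time", and with reduced variance. Endpoint determination and sample size calculation works from log time and concludes "We could therefore expect to detect a difference of around 21 days in mean time to best visual acuity". Analyses equates the primary objective with a comparison of time to best acuity. Its t tests are there "to compare length of time and compliance", and Levene's test is for variance in time.
- **Acuity.** Primary outcome and its measurement names logMAR acuity as the primary outcome variable.

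In Personalized dosing strategy, "it is assumed that the total effective dose is dose-rate independent". The same section holds that "any dose received by a patient in excess of this total effective dose is" wasted.

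Hours appear elsewhere as monitor data (Occlusion dose monitoring) and as a predictor of acuity change (Analyses). They may also enter through compliance, a secondary comparison whose measure is not defined. The Discussion names less treatment as a significant potential benefit and links it to how unpleasant patching is for children.

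**The concern.** The two arms prescribe different hours per day by design. If the dose needed is the same at any dose-rate, time to best acuity is that dose divided by the hours worn per day, and the hours needed to get there are equal in both arms. Any saving lies in dose worn beyond the total effective dose, which shows only in cumulative hours at trial endpoint.

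A clear time result could therefore arise with almost the same hours worn in both arms, and a null time result could arise while hours fall. The trial could then report against the abstract's objective, or claim less treatment as in the Discussion, without having compared the amount of treatment.

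**Working it through.** **1. The plan's own figure is in days.** From the sample size section: log time has mean 4.0133 and SD 0.801, and d = 0.605. Then exp(4.0133) = 55.3 days, exp(4.0133 − 0.605 × 0.801) = 34.1 days, and the difference is 21.2 days. This reproduces the stated 21 days. No mean, SD or detectable difference in hours is given.

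**2. Total effective dose D\*.** The formula is in Personalized dosing strategy. The age coefficient is read as 0.135, the reading that gives the protocol's own 389 h. The child is the worked example (48 months, residual amblyopia 0.5 logMAR), taken as each amblyopia type in turn.

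- Anisometropic: (18.150 + 16.122 × 0.5 − 0.135 × 48)² = 19.731² = 389.3 h
- Mixed: (19.731 − 0.547 − 12.176 × 0.5 + 0.065 × 48)² = 16.216² = 263.0 h
- Strabismic: (19.731 − 8.028 − 11.334 × 0.5 + 0.192 × 48)² = 15.252² = 232.6 h

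**3. Dosing rules.**

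- *Personalized:* outstanding dose divided by the days left of 84, with a 14-day horizon from week 10, rounded up to the next half hour, updated every two weeks. Because "dose-rates less than 2 hours per day are never prescribed", the prescription falls to 2 h/day once D\* is met.
- *Standardized:* fixed at 3 h/day, assuming amblyopic-eye acuity in the moderate band (0.4 to <0.8 logMAR).

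At full wear the anisometropic child's personalized prescriptions per two-week block are 5, 5, 4.5, 4.5, 4.5, 4.5, then 2 h/day.

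**4. Exit rules.** Equal-acuity exit is the first two-weekly visit at or after D\*. Stability exit, "remaining unchanged over three consecutive visits", is taken as that visit plus two more, so 28 days later in either arm.

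**5. Results, personalized v standardized (ratio), D\* equal in both arms.** The latent day is when D\* is crossed. The visit day is when that can first be recorded.

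| Wear, type | Latent day | Visit day | Hours, equal-acuity exit | Hours, stability exit |
|---|---|---|---|---|
| Full, anisometropic | 83 v 130 (0.64) | 84 v 140 (0.60) | 392 v 420 (0.93) | 448 v 504 (0.89) |
| Full, mixed | 83 v 88 (0.95) | 84 v 98 (0.86) | 266 v 294 (0.90) | 322 v 378 (0.85) |
| Full, strabismic | 82 v 78 (1.06) | 84 v 84 (1.00) | 238 v 252 (0.94) | 294 v 336 (0.88) |
| Half, anisometropic | 130 v 260 (0.50) | 140 v 266 (0.53) | 399 v 399 (1.00) | 427 v 441 (0.97) |
| Half, mixed | 123 v 175 (0.70) | 126 v 182 (0.69) | 266 v 273 (0.97) | 294 v 315 (0.93) |
| Half, strabismic | 121 v 155 (0.78) | 126 v 168 (0.75) | 238 v 252 (0.94) | 266 v 294 (0.90) |

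If the stability rule means three further visits, the full-wear anisometropic child has 476 v 546 h (0.87).

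The half-wear rows have no upper limit on the prescription, since the protocol states none. The anisometropic child's prescription then reaches 12 h/day in the block before week 12. With an assumed cap of 6 h/day, latent time ratios become 0.58, 0.72 and 0.80, and hours ratios run from 0.89 to 1.01.

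**6. Precision of an hours comparison.** The documents give no SD for log hours, so 0.4 to 1.0 is assumed. With 60 per arm (two-sided 5%, 118 df), 80% power needs d = 0.516:

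- detectable ratio: exp(−0.516 × SD) = 0.81 to 0.60
- 95% CI factor: exp(1.980 × SD × √(2/60)) = 1.16 to 1.44

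**The case against.** The strongest reply is that the slip is one abstract sentence. The objectives, power basis and analysis agree on time, and the abstract's own Discussion paragraph speaks of duration. Nothing in conduct or in the primary test has to change, and a secondary hours analysis may sit in an analysis plan that is not shown. Much of this stands. The time test is valid for duration, because dose-rate is part of each strategy, and details such as scale or the exact compliance measure belong in the analysis plan. What that plan cannot settle is an article that gives two primary objectives and a third quantity as primary outcome.

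A second reply is that the compliance t test may already compare hours. It might: the Discussion glosses compliance as the dose actually received. The worked example, however, sets 30 h received against 70 h prescribed. The test cannot be relied on to compare total hours.

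Three stronger readings are tempting, and the documents do not support them.

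- *Time and hours move in opposite directions.* The strabismic child at full wear is 6% slower only on the latent day. Acuity is recorded every two weeks, and on that clock the arms tie at day 84. At half wear, time favours the personalized arm for all three types. Half wear is closer to the Discussion's statement that less than half the prescribed occlusion is received.
- *The personalized arm uses more hours.* Holding 5 h/day for 28 days past D\* would give 529 v 473 h, but the updating rule drops the prescription to 2 h/day once D\* is met. The one ratio above 1 (1.01) needs the assumed 6 h/day cap.
- *The trial tests the wrong thing.* Most of the methods text specifies time, and the documents do not show that hours were the intended primary measure.

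**Conclusion.** The concern holds as an inconsistency with a practical consequence, and it should be fixed. The stated primary objective (hours), the powered and tested quantity (time) and the named primary outcome (logMAR acuity) differ. Under the protocol's own model, a time result cannot support a claim of fewer hours or less treatment.

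The size depends on amblyopia type and wear. At full wear, a 40% shorter visit time goes with 7% to 11% fewer hours for the anisometropic child, and no difference in visit time goes with 6% to 12% fewer for the strabismic child. At half wear, time falls by 22% to 50% while hours fall by 0% to 10%, so time overstates any saving.

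These are illustrations for one age and severity, with no case mix. They rest on an equal D\* in both arms, dose-rate independence (which the protocol adopts to keep the model simple), uniform wear and the moderate acuity band. They show that time is no proxy for hours and do not predict the trial's result.

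**What to change.** Keep both dosing rules, the sample size and the time test, and make four changes.

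1. **Abstract, Methods/design:** restate the primary objective as in Objectives of the study, that is, reaching optimal acuity sooner and with less variance.
2. **Primary outcome and its measurement:** name time to best visual acuity as the primary outcome, with logMAR acuity as the measurement from which it is derived.
3. **Analyses:** add a secondary between-arm estimate, with 95% CI, of cumulative monitor-recorded hours at trial endpoint. Show it beside endpoint acuity by arm, so that fewer hours with worse acuity is not read as a saving.
4. **Discussion:** let any claim of less treatment rest on that estimate, and limit a time result to shorter duration.

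The cost is a few sentences and one more analysis. The monitor already records every child in the occlusion phase, so no visits or patients are added. The downside is limited precision. The illustrated endpoint-hours ratios without a cap (0.85 to 1.00) are closer to 1 than the 0.81 to 0.60 that 60 per arm could detect with 80% power under the assumed SDs. The result should be read as an estimate and not as a confirmatory test, and it may support a more modest claim than the abstract now makes.

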**Discussion:**

This is the first randomized controlled trial of occlusion therapy for amblyopia to compare a treatment arm representative of current best practice with an arm representative of an entirely novel treatment regimen based on statistical modelling of previous trial outcome data. Should the personalized dosing strategy demonstrate superiority over the standardized dosing strategy, then its adoption into routine practice could bring practical benefits in reducing the duration of treatment needed to achieve an optimal outcome.

**Trial registration:**

ISRCTN ISRCTN12292232.

## Background

Amblyopia is the commonest visual disorder of childhood in developed nations, with an estimated prevalence of 1.6 to 3.5% [1]. Principally manifesting as a deficit of visual acuity in one eye, it is most commonly found in association with squint or anisometropia (unequal refractive error between eyes), or both. Historically, a diverse range of physical and pharmacological treatments have been prescribed [2], and although novel treatments continue to emerge (for example, those involving visual stimulation) [3-5], occlusion of the nonamblyopic eye, most commonly by an adhesive fabric patch, remains the treatment of preference [6].

For the most part of the twentieth century, the efficacy of occlusion went unquestioned and it was only with the championing of evidence-based medicine in the 1990s [7] that its effectiveness became the subject of systematic investigation [2,8]. One strand of observational research has sought to determine mathematically the relationship (‘dose response’) between the amount of patching and any subsequent change in visual acuity. Such studies were facilitated by the introduction of the occlusion dose monitor by Fielder and colleagues in 1994 [9,10]. This device permitted, for the first time, objective records of patching episodes to be obtained from children undergoing treatment. Using this device, two principal studies, MOTAS and ROTAS [11,12], have provided insight into the dose-response relationships of occlusion therapy and how these vary as a function of amblyopia type, age of patient, and severity of the condition. The findings of these studies have largely been confirmed by traditional randomized trials [13] and have helped to identify optimal treatment regimens for use in clinical practice.

A practical consequence of this research has been a trend away from *ad-hoc* patching regimens (anything from a few minutes per day up to all waking hours) towards a more standardized approach (now gradually being incorporated into practice guidelines [14]). Thus, it is now possible to elicit consensus among expert practitioners as to what presently constitutes best practice, that is, in the amount of patching that should be prescribed to an initially presenting amblyopic child. In this Randomized Occlusion Dosing Strategies (RODS) trial, the occlusion regimens prescribed in one of the treatment arms (the standardized dosing strategy) represents the current prevailing clinical opinion of a representative group of UK orthoptists.

The rationale behind RODS is the notion that further refinements in prescribing may yield improvements in outcome. By examining the dose-response relationships determined for the amblyopic children taking part in MOTAS [11] and ROTAS [12], we have generated a statistical model that allows us to estimate, on the basis of the severity of the initially presenting amblyopia, the age of the patient, and the type of amblyopia, the amount (total hours) of occlusion required to treat any given amblyopic child. This we term the ‘total effective dose’, which for any given treatment period can be converted into a daily dose-rate (hours per day) and subsequently increased or decreased depending on compliance. We term this approach a ‘personalized dosing strategy’.

In summary, the protocol described herein has been designed to test the hypothesis that superior clinical outcomes will be obtained with a personalized dosing strategy compared with a standardized dosing strategy (in which all patients receive an occlusion regimen based upon current best practice).

## Methods/design

### Objectives of the study

The primary study objective is to determine whether study participants in receipt of a personalized dosing strategy reach trial endpoint (optimal visual acuity) in a shorter period of time, and with reduced variance, than those in receipt of a standardized dosing strategy.

The secondary study objectives are:To determine the relationship between observed changes in logMAR visual acuity as a function of:Objectively monitored occlusion dose,Type of amblyopia,Age of participant.To determine whether compliance differs between standardized and personalized dosing strategy treatment arms.

### Eligibility criteria

#### Inclusion criteria

Male or female,Aged 3 to 8 years inclusive,Visual acuity of 0.10 logMAR or higher (poorer acuity) in the worst (amblyopic) eye,Interocular difference in acuity of at least 0.20 logMAR,Presence of anisometropia or strabismus (or both),Knowledge of the extent of spectacle wear (if any) prior to trial entry,Parent or guardian willing and able to give informed consent for participation in the study,Cognitive, motor and verbal skills of sufficient maturity to undergo visual acuity testing with letter optotypes.

#### Exclusion criteria

Comorbid ocular disease (including amblyopia associated with form deprivation),Prior occlusion therapy for amblyopia,Evidence of learning difficulties or developmental delay.

### Study design

The study is a randomized, parallel group, unmasked design, as depicted in Figure 1. Each study arm comprises three sequential phases: initial assessment, optical treatment (common to each respective study arm) and occlusion (either standardized or personalized dosing strategy in respective study arms).

**Figure 1 Fig1:**
[figure not shown]
Study participant flow.

### Dosing strategies

#### Standardized dosing strategy

In the standardized dosing strategy arm, participants are prescribed one of three dosing regimens dependent on their visual acuity at the end of the optical treatment phase. These dosing regimens were the consensus outcome, initially of formal face-to-face discussion, between eight senior orthoptists identified by membership of the British and Irish Orthoptic Society, and drawn from geographically diverse areas of the United Kingdom. All experts had a minimum of 10 years’ clinical experience. Discussion focused on the management of six clinical scenarios representative of cases meeting the RODS eligibility criteria. The experts’ views of how each scenario should be managed were appraised by the panel convener ([name]) and a series of dosing regimens was derived. These regimens were subsequently reviewed by the panel and their suitability unanimously confirmed by all members as follows:Mild amblyopia (<0.4 logMAR): 2 hours per day,Moderate amblyopia (0.4 to <0.8 logMAR): 3 hours per day,Severe amblyopia (≥0.8 logMAR): 5 hours per day.

